**Exclusion criteria**

(1)Individuals who received three doses of the BNT162b2 mRNA vaccine at the time of obtaining informed consent.(2)Pregnant women, women who are potentially pregnant, women who wish to become pregnant before completing the post-test, and breastfeeding women.(3)Individuals with fibrodysplasia ossificans progressiva.(4)Individuals with underlying diseases, such as serious cardiovascular disease, kidney disease, liver disease, blood disease, developmental disorders, respiratory diseases, and diabetes mellitus.(5)Individuals with convulsion in the past.(6)Individuals with a previous diagnosis of immunodeficiency and those with relatives with congenital immunodeficiency.(7)Individuals who may be allergic to the ingredients of KD-414.(8)Individuals who have participated in another clinical trial within the past four months (120 days) from the date of proposed vaccination with KD-414 and who have received other test substances (excluding placebo), or who are scheduled to participate in another clinical trial during the study period.(9)Individuals who have received blood transfusions or gamma globulin products within the past three months (90 days) or have received high-dose gamma globulin products (200 or more mg/kg bodyweight) within the past six months (180 days) from the date of proposed vaccination with KD-414.(10)Patients who have received radiotherapy, immunosuppressive drugs (topical drugs are available), immunosuppressive therapy, antirheumatic drugs, adrenocorticotropic hormones, or corticosteroids that affect immune function within six months (180 days) after the date of vaccination (if the total daily dose of prednisolone was ≥2 mg/kg bodyweight and the treatment duration was ≥14 days, topical drugs may be used).(11)Individuals immunized with the live vaccine within one month or inactivated vaccine within one week.(12)Individuals with a history of breakthrough infection who wish to be immunized with KD-414.(13)Individuals judged by the investigator (or sub-investigator) to be ineligible for the study.

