**Therapies prohibited before and during the**
**study period**

(1)Immunization with other COVID 19 vaccines is prohibited for 40 days post-KD-414 vaccination.(2)Other vaccines are not allowed for 7 days post-KD-414 vaccination.

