**Target sample size and rationale**

Target number of subjects receiving KD-414 to evaluate the main hypothesis: 60 subjects

Target sample size for this study: 97 patients

Rationale: Determining if the antibody titer after the booster dose (KD-414) was lower than that after the second dose of BNT162b2 mRNA. The IgG-S antibody titer after the administration of the second dose of BNT162b2 mRNA vaccine will be investigated because the data for neutralizing antibody titers evaluated using the assay used in this study are not available. The titers of IgG-S and neutralizing antibodies are reported to be highly correlated. We assume that the titer of IgG-S after immunization with KD-414 is similar to that after immunization with the second dose of BNT162b2 mRNA in this study population (4.25 (standard deviation; SD 0.35) on a log_10_ scale). The World Health Organization guidelines on vaccine development set a geometric mean titer (GMT) ratio of 0.67 as the threshold for testing non-inferiority. In the case that the lower limit of the 95% confidence interval for the GMT of IgG-S for the KD-414 to that of Pfizer vaccine is >0.67, the antibody titer after the booster of KD-414 is not inferior to the second dose of BNT162b2 mRNA. Based on these assumptions, the required sample size for 90% power would be 45 for an SD of 0.35, whereas it would be 58 for an SD of 0.4 (Table 5).

The main objective of this study is to obtain consent for immunization with KD-414 from 97 patients with titer test results up to the second dose. Although the rate of informed consent is unknown, the target sample size will be 60 to determine 58 post-vaccination titer values after immunization with KD-414. However, even if the number of subjects enrolled is below 60, a certain power will be assured.

Additionally, patients who do not agree to receive KD-414 (consented to participate in this study) will also be enrolled to compare the antibody titers of non-vaccinated subjects with KD-414 with those of vaccinated subjects. The target sample size for non-vaccinated and vaccinated cases combined will be 97 patients who participated in the previous study.

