**Primary endpoint analysis**

Primary analysis

The geometric mean of the neutralizing antibody titers will be calculated for PPS cases on day 7 post-inoculation. Meanwhile, the geometric mean ratio of the neutralizing antibody titer at day 7 post-BNT162b2 mRNA vaccination to the geometric mean value and the 95% confidence interval calculated in the previous study (“*A survey of vaccine-induced COVID-19 antibody titer to verify temporal change*”: NCGM Ethical Review Board Approval Number: NCGM-A-004175-04) will be used.

Secondary analysis for the primary endpoint
(1)The geometric mean of the neutralizing antibody titer on day 7 against day 0 will be calculated for PPS cases. Additionally, the geometric mean of neutralizing antibody titers in non-vaccinated subjects on day 40 will be calculated. The geometric mean ratio of neutralizing antibody titers in vaccinated subjects to that in non-vaccinated subjects among PPS cases will also be calculated.(2)The percentage of cases in which the geometric mean ratio of neutralizing titers on day 7 to those on day 0 was ≥4 will be calculated.(3)Subgroup analyses will be performed on the following items for test drug-vaccinated and non-vaccinated cases among PPS cases:

▪Work history (presence or absence of work-related contacts)▪Sex (male/female)▪Age (below or above the median)▪Medical history▪Interval between the third dose and the second dose of the BNT162b2 mRNA vaccine.▪By variant
(4)Among PPS cases, the geometric mean neutralizing antibody titer on day 7 will be calculated for unvaccinated cases. Additionally, if the non-vaccinated subject received the third dose of other vaccines, the geometric mean of neutralizing antibodies on day 7 after the third dose of other vaccines will be calculated.(5)Among PPS cases, the geometric mean neutralizing antibody titers on day 7 will be calculated for unvaccinated and vaccinated cases and compared using the Wilcoxon rank-sum test. Additionally, the geometric mean ratio of neutralizing antibodies on day 7 post-third dose of other vaccines against the vaccinated subject and the 95% confidence interval will be calculated for non-vaccinated subjects.

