## Figures and Tables

**Figure 1 life-12-00966-f001:**
[figure not shown]
Flowchart of study recruitment process.

**Table 1 life-12-00966-t001:** Study calendar (KD-414 group).

Visit			Visit 1			Observation period	Visit 2	Visit 3
			KD-414 inoculation				Post hoc observation	Post hoc observation
Expiration day (Day) * 1		Obtaining written consent	Day 0			Days 1–7	Day 7	Day 40
[Acceptable range]			Pre	Inoculation	After		[±1 day]	[±1 day]
Medical institutions	KD-414 inoculation			◯				
	Examination		◯		△ * 2		◯	◯
	Body temperature measurement		◯					
	Volume of blood sampling		17 mL				22 mL	17 mL
	Immunogenicity		◯				◯	◯
Home	Observation of adverse events					◯	◯	◯
	(Health diary entries)							

◯: Essential, △: Occurrence of an adverse event. * 1: The day of immunization with KD-414 will be considered day 0. * 2: Performed at 15–30 min post-vaccine inoculation.

**Table 2 life-12-00966-t002:** Study calendar (KD-414 non-vaccinated).

Visit			Visit 1	Visit 2	Visit 3
Expiration Day (Day) * 1		Obtaining written consent	Day 0	Day 7	Day 40
[Acceptable range]				[±1 day]	[±1 day]
Medical institutions	Volume of blood sampling			19 mL	14 mL
	Immunogenicity			◯	◯

◯: Essential. * 1: The day of KD-414 inoculation is considered day 0.

**Table 3 life-12-00966-t003:** Study calendar (public cost booster).

Visit		Visit 1	Observation period	Visit 2	Visit 3
Expiration Day (Day) * 1		Day 0	Day 1–7	Day 7	Day 40
[Acceptable range]				[±1 day]	[±1 day]
Medical institutions	Public cost vaccination	◯			
	Examination	◯		◯	◯
	Body temperature measurement	◯			
	Volume of blood sampling	17 mL		22 mL	17 mL
	Immunogenicity	◯		◯	◯
Home	Observation of adverse events	◯	◯	◯	◯
	(Health diary entries)				

◯: Essential. * 1: The day of public cost vaccination date was considered day 0.

**Table 4 life-12-00966-t004:** Evaluation criteria for determination by reagents.

Outcome		Determination	
		Positive	Negative
①	Determination of neutralizing antibodies against live SARS-CoV-2 virus (fold)	≥40	<40
②	Antibody (IgG) titers against the viral nucleocapsid protein (Index or S/C)	≥1.40	<1.40
③	Antibody (IgM) titers against viral spike proteins (Index or S/C)	≥1.00	<1.00
④	Antibody (IgG) titers against viral spike proteins (AU/mL)	≥50.0	≥50.0

**Table 5 life-12-00966-t005:** Power calculations.

	Detection Power 80%	Detection Power 85%	Detection Power 90%
SD 0.35	34	39	45
SD 0.40	44	50	58

**Table 6 life-12-00966-t006:** Classification of severity of local reactions (inoculation site).

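### The comparison of KD-414 recipients with people who declined it is unadjusted and excludes prior infection on one side only

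*Protocol article*

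**What the plan says.** **How the comparator arises.** Under Target sample size and rationale, "patients who do not agree to receive KD-414 (consented to participate in this study) will also be enrolled". The total target is 97, of whom 60 are to receive KD-414.

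**Prior infection.** Exclusion criterion (12) reads "Individuals with a history of breakthrough infection who wish to be immunized with KD-414". No matching criterion applies to people who decline the vaccine.

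**The test.** Item (5) of the secondary analyses for the primary endpoint says that day-7 geometric mean neutralizing titres in the per-protocol set "will be calculated for unvaccinated and vaccinated cases and compared using the Wilcoxon rank-sum test". No covariate or stratification is named. Under Analysis of the secondary variables, similar analyses are applied to the other immunogenicity endpoints.

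**Item (1) of the same list.** After a day-7 versus day-0 contrast, "the geometric mean of neutralizing antibody titers in non-vaccinated subjects on day 40 will be calculated". Then: "The geometric mean ratio of neutralizing antibody titers in vaccinated subjects to that in non-vaccinated subjects among PPS cases will also be calculated". That ratio has no stated day.

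**Day 0.** The footnote to Table 2, the calendar for the non-vaccinated, says "The day of KD-414 inoculation is considered day 0". Table 2 gives this group blood draws on days 7 and 40 and none on day 0.

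**Data in hand.** Inclusion criterion (1) requires a completed antibody measurement at day 7 after dose 2. The sizing section gives the IgG-S mean and SD after dose 2 in this population. Age, sex and vaccination dates are listed under Subject characteristics.

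**The concern.** Accepting or declining an unapproved booster is a personal choice. It may go with age, work exposure, earlier response to BNT162b2 or past infection, and any of these can shift a titre without KD-414 doing anything. A rank test on the raw titres cannot separate such differences from the vaccine effect.

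The exclusion rule adds an imbalance by design. People with breakthrough infection may stay among the non-vaccinated but cannot enter the vaccinated group.

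The planned background table and the subgroups in item (3) do not solve this. Item (3) lists neither the dose-2 titre nor prior infection as such, and neither step yields an adjusted between-group estimate.

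At stake is how to read the contrast between recipients and concurrent non-recipients. The primary comparison with dose-2 titres is not affected.

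**Working it through.** **1. The plan's own figure.** The protocol gives no size or power for this group comparison. Its Table 5 covers the dose-2 comparison only. With margin −log10(0.67) = 0.1739, true difference 0 and one-sided alpha 0.025, the normal approximation at 90% power is

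- SD 0.35: (0.35 × 3.2415 / 0.1739)² = 42.6, so 43
- SD 0.40: (0.40 × 3.2415 / 0.1739)² = 55.6, so 56

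The one-sample t version (noncentral t) gives 45 and 58, and reproduces all six cells of Table 5.

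**2. Precision of the group comparison.** Assume all 97 enrol and 60 accept, leaving 97 − 60 = 37. Take the SD of 0.35 from the sizing section. That is an IgG-S SD after dose 2, borrowed here for neutralizing titres.

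- SE = 0.35 × √(1/60 + 1/37) = 0.0732 log10
- 95% CI factor = 10^(1.96 × 0.0732) = 1.39
- Difference detectable with 80% power = 0.205 log10, or 1.60-fold (0.234, or 1.71-fold, at SD 0.40)

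**3. One-sided infection rule.** If k of 37 comparators have titres f times higher, the comparator geometric mean is multiplied by f^(k/37). Assume f = 10.

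- k = 2: 10^(2/37) = 1.13
- k = 4: 10^(4/37) = 1.28

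The ratio of vaccinated to non-vaccinated is then multiplied by 1/1.13 = 0.88 or 1/1.28 = 0.78. Both k and f are assumptions.

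**4. Selection.** Simulation of 60 versus 37 with no KD-414 effect, an assumed correlation of 0.6 between dose-2 and day-7 titre, and 4,000 runs per setting. The groups differ only through the dose-2 titre. Rejection at nominal 5%:

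| Day-7 difference (log10) | Rank-sum, SD 0.35 | Rank-sum, SD 0.40 |
|---|---|---|
| 0 | 4.7% | 5.4% |
| 0.05 | 10% | 9% |
| 0.10 | 26% | 21% |
| 0.15 | 51% | 42% |
| 0.20 | 74% | 64% |

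A linear model adjusted for the dose-2 titre stays at 4.7% to 5.5% throughout. A day-7 difference of 0.10 (1.26-fold) corresponds here to a dose-2 difference of 0.10/0.6 = 0.167 log10 (1.47-fold). The adjusted model does well partly by construction, because the simulated selection acts only through the covariate.

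**5. Precision gained.** Adjustment multiplies the SE by √(1 − r²).

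- r = 0.5: 10^(1.96 × 0.0732 × 0.866) = 1.33
- r = 0.7: 10^(1.96 × 0.0732 × 0.714) = 1.27

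The protocol calls IgG-S and neutralizing titres highly correlated but gives no coefficient, and none between dose-2 IgG-S and a later neutralizing titre. So r is assumed.

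**The case against.** The study is exploratory and described as single-arm. The Discussion names the lack of randomisation as a limitation, and both the sizing and the primary analysis concern the dose-2 comparison. Background factors are tabulated by group, subgroups by age and sex are planned, and a separate analysis plan may add adjusted models. If many non-vaccinated titres lie below the assay limit (the positivity cut-off in Table 4 is 40), a rank test is the more robust tool. All of this limits the weight of the point, and the last argument is a reason to keep the Wilcoxon test. None of it removes the point: the protocol itself names the unadjusted test and words the infection exclusion for one group.

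Stronger readings are tempting, and the documents do not support them:

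- *The rank test compares different sampling days.* It does not. Item (5) uses day 7 in both groups, and Tables 1 and 2 schedule both on days 7 and 40, ±1 day.
- *The ratio in item (1) is day 7 against day 40.* That is an inference, since no day is given. Any waning loss computed from it would also need a half-life that the protocol does not supply.
- *Time since dose 2 differs materially between groups.* The Table 2 footnote is unusable as worded, but both groups come from one hospital cohort and no such difference is shown.
- *People boosted at public expense count in the non-vaccinated day-40 mean.* The ban, "Immunization with other COVID 19 vaccines is prohibited for 40 days post-KD-414 vaccination", indeed binds only recipients. But items (4) and (5) treat other third doses separately, Table 3 resets day 0, and the Discussion places public vaccination 42 days after KD-414. At most a sentence on later samples is absent.
- *A dose-2 neutralizing titre exists for everyone.* The required measurement is an antibody titre. Neutralizing titres in the study assay were unavailable at planning and depend on residual samples.

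**Conclusion.** The point holds for the unadjusted test and the one-sided infection exclusion. Together they make the day-7 contrast between recipients and decliners a mixture of vaccine effect, selection and prior infection. The net direction cannot be determined. Infection retained only in the comparator would tend to understate KD-414, while self-selection could act either way.

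The sizes are illustrations, not estimates: 13% to 28% inflation of the comparator mean, a false-positive rate of 21% to 26% at a selection-driven day-7 difference of 0.10 log10, and a CI factor falling from 1.39 to between 1.33 and 1.27. They rest on a 60/37 split, a borrowed SD, and assumed numbers infected, fold rise and correlations.

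The unstated day in item (1) and the day-0 anchor in Table 2 are wording points to reconcile. The change is worth making because it is cheap, but it concerns a secondary analysis.

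**What to change.** 1. Make the main between-group estimate a linear model of log10 neutralizing titre on group, day-matched (day 7 with day 7, day 40 with day 40). Adjust for log10 IgG-S at day 7 after dose 2, days since dose 2, age and sex. Report the adjusted geometric mean ratio with its 95% CI.
2. Keep the Wilcoxon test as a sensitivity analysis, which also helps if many titres fall below the assay limit.
3. Apply one prior-infection rule to both groups in this analysis: recorded history, or IgG-N of 1.40 or more at the first available study sample. That is day 0 in recipients and day 7 in the non-vaccinated, who have no day-0 draw. Screening one group at any visit and the other only at day 0 would create a new one-sided exclusion. Later IgG-N in recipients is hard to use, since KD-414 is a whole-particle vaccine and may itself raise it.
4. State the day of the ratio in item (1), and give the non-vaccinated a calendar anchor for day 0.

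Cost: protocol or analysis-plan wording and a little analysis, with no new samples. A few non-vaccinated participants may leave this comparison, and the seven-day gap between screening samples remains. The result stays observational, since adjustment does not remove unmeasured selection.

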In March 2021, at public expense, the National Center for Global Health and Medicine (NCGM) conducted an observational study of 100 healthcare volunteers from NCGM staff vaccinated with the BNT162b2 mRNA vaccine (Pfizer-BioNTech). The antibody titers were monitored for nine months (*A survey of vaccine-induced COVID-19 antibody titer to verify temporal change*; NCGM Ethical Review Board Approval Number: NCGM-A-004175-04). An in-depth evaluation of the primary immunization revealed that the highest antibody titers were observed on day 7 post-second dose (day 28 post-first dose), which gradually declined thereafter [3,4].

A previous study has shown that a third dose with CoronaVac, an inactivated vaccine, given eight months after a second dose with CoronaVac, significantly increased neutralizing antibody concentrations against SARS-CoV-2 in healthy adults aged 18 years and older [5]. Another study investigated the reactogenicity and immunogenicity of seven different COVID-19 vaccines, including inactivated vaccine (VLA2001), as a third dose after two doses of ChAdOx1 nCov-19 or BNT162b2, showing that the immunogenicity of homologous or heterologous third dose booster vaccination with all tested vaccines was superior to control (quadrivalent meningococcal conjugate vaccine) regardless of which vaccine had been received during the initial course [6]. This suggests that many types of third booster dose are efficacious and supports the potential use of a booster dose of “KD-414”, a novel Japanese inactivated vaccine.

KD-414 is an inactivated vaccine against SARS-CoV-2 being developed by KM-Biologics Co., Ltd. (Kumamoto, Japan). It is an inactivated whole-particle vaccine containing aluminum hydroxide added as an immune aid after growth of SARS-CoV-2 on Vero cells from African green monkey kidney and purification and inactivation of the virus. Currently, Phase I/II clinical trials have been completed in Japan and have shown efficacy of KD-414 in adults and the elderly, and that adverse reactions are comparable to general inactivated vaccines with fewer adverse reactions than for mRNA vaccines. It is thought that KD-414 could provide a new option for those who have difficulty with existing vaccinations or who require higher levels of safety.

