**Content of clinical research**

Type of clinical trial

Open-label, single-arm study.

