**Specific methods (including schedules)**

The study will be conducted according to the schedules shown in Table 1, Table 2 and Table 3 and the recruitment process is shown in Figure 1.

If a third dose of BNT162b2 mRNA is received in the future at public expense, the immunogenicity-related parameters and adverse events will be recorded on days 0, 7, and 40 post-vaccination.

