**Investigation items for immunogenicity endpoints**

(1)Timing of blood sampling: Visits 1 (before vaccine inoculation), 2, and 3.(2)Measurements:

Determination of neutralizing antibody titers against live SARS-CoV-2 viruses (on days 0, 7, and 40 post-inoculation and in the residual sample collected on days 7 and 40 in the previous studies; conducted at the Department of Refractory Viral Infections, National Center for Global Health and Medicine Research Institute, Tokyo, Japan).

①Determination of neutralizing antibodies (on days 0, 7, and 40 post-inoculation) against live SARS-CoV-2 virus (in residual samples collected on days 7 and 40 in previous studies; conducted by the Department of Refractory Viral Infections, National Center for Global Health and Medicine Research Institute, Tokyo, Japan) is shown in Table 4.

Three assays were performed to detect the IgM and IgG antibodies against SARS-CoV-2 spike protein (IgM-S and IgG-S, respectively) and IgG antibodies against SARS-CoV-2 nucleocapsid protein (IgG-N). The presence of IgG-N antibodies can indicate SARS-CoV-2 infection prior to the study and during follow-up, regardless of the BNT162b2 vaccination status. In contrast, the presence of IgM-S and IgG-S indicates previous infection and/or humoral immunity following BNT162b2 vaccination, because BNT162b2 is constructed to express the full-length spike protein.

②Antibody (IgG) titers against the viral nucleocapsid protein

The Abbott ARCHITECT^®^ SARS-CoV-2 anti-N IgG assay based on semi-quantitative CMIA was performed. Determination by reagent is shown in Table 4 (determination on days 0, 7, and 40 post-inoculation)

③Antibody (IgM) titers against viral spike proteins

The AdviseDx SARS-CoV-2 IgM assay, based on semi-quantitative CMIA, was performed using the Abbott ARCHITECT^®^ according to the manufacturer’s instructions. Determination by reagent is shown in Table 4.

④Antibody (IgG) titers against viral spike proteins

The AdviseDx SARS-CoV-2 IgG II assay was performed using the Abbott ARCHITECT^®^ following the manufacturer’s protocol. Determination by reagent is shown in Table 4.

⑤Flow cytometric analysis of Th1 and Th2 cells (in samples collected on day 7 post-inoculation) (outsourced to SRLs, Tokyo, Japan).

The percentage of Th1 (IFNγ^+^ and IL-4^−^) and Th2 (IFNγ^-^ and IL-4^+^) cells among CD4^+^ lymphocytes will be calculated.

⑥QuantiFERON SARS-CoV-2 RUO test (QIAGEN, Germany; performed on days 0 and 7 post-inoculation)

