## 3. Discussion

The COVID-19 pandemic is currently ongoing, and there have been significant efforts in the development of COVID-19 vaccines. However, the neutralizing antibody titers in vaccinated individuals are reported to progressively decrease over time. Japanese pharmaceutical companies have published the results of Phase I and II studies on the safety and efficacy of different vaccines. Final clinical trials will be conducted with the aim of practical application by March 2023. Since mRNA vaccination is progressing around the world, it is necessary to evaluate the efficacy and safety of booster doses in individuals who have received two doses of mRNA vaccine in order to make effective use of inactivated vaccines in the future. There have been studies evaluating the progression of antibody titers with boosters with inactivated vaccines after initial immunization with inactivated vaccines and with boosters with mRNA vaccines, but few studies have evaluated boosters with inactivated vaccines after initial immunization with mRNA vaccines [12,13]. This is the first study of booster immunization with KD-414 developed in Japan.

This manuscript describes the protocol for a study that aims to examine the effect of a booster dose with KD-144, a novel inactivated Japanese vaccine, on antibody titers. A previous study comparing the efficacy, side effects, and seroconversion of various vaccine formats against SARS-CoV-2, including inactivated, recombinant, mRNA, and nano-particle-based vaccines suggested that inactivated vaccines have fewer side-effects and similar seroconversion compared to other types of vaccines [14]. Furthermore, heterologous prime-boost vaccine strategies have been shown to result in improved immunogenicity, reactogenicity, safety, effectiveness and flexibility, as well as to mitigate against intermittent supply shortages [15,16].

There are some limitations to this protocol. First, it is designed as a single-arm study with no randomization. Second, the follow-up period will be relatively short (40 days) because the COVID-19 vaccination at public expense commences 42 days after KD-414 vaccination. Third, the definition of an ‘appropriate’ amount of KD-414 vaccination is unclear; the dose used in this study was determined based on the dose of the first and second shots of KD-414 in Phase I and II clinical trials.

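### The secondary ratio of day-7 titres between KD-414 and another third dose omits the day-0 titre taken in both booster groups, so it is liable to confounding in favour of KD-414

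*Protocol article*

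**What the plan says.** The point concerns the protocol article, Primary endpoint analysis, secondary analysis item (5). Its first sentence compares KD-414 recipients with undosed participants by a rank-sum test. Its second sentence compares two boosters, among participants who did not take KD-414 but later had another third dose, through "the geometric mean ratio of neutralizing antibodies on day 7 post-third dose of other vaccines against the vaccinated subject and the 95% confidence interval". No covariate is named.

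- **Pre-dose titre, KD-414 group.** Investigation items for immunogenicity endpoints gives "Timing of blood sampling: Visits 1 (before vaccine inoculation), 2, and 3" and "Determination of neutralizing antibody titers against live SARS-CoV-2 viruses (on days 0, 7, and 40 post-inoculation". Table 1 marks the day-0 sample as essential.
- **Pre-dose titre, public-cost booster.** Specific methods says "the immunogenicity-related parameters and adverse events will be recorded on days 0, 7, and 40 post-vaccination". Table 3 marks day-0 immunogenicity as essential.
- **Undosed participants.** Table 2 has no day-0 sample.
- **Allocation.** The study is an "Open-label, single-arm study", and the target sample size section enrols people who decline KD-414 for comparison.
- **Timing.** The Discussion says "the COVID-19 vaccination at public expense commences 42 days after KD-414 vaccination". The Background says that titres peaked seven days after dose 2, "which gradually declined thereafter".
- **Day 0 and timing elsewhere.** Item (1) says "The geometric mean of the neutralizing antibody titer on day 7 against day 0 will be calculated for PPS cases". Item (2) takes the share with at least a fourfold rise, and item (3) has a subgroup by the interval between doses 2 and 3.

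**The concern.** A day-7 titre after a booster reflects both the level before the dose and the response to it. If one group is boosted later in the decline after dose 2, it is likely to start lower. A plain ratio of day-7 geometric means then attributes that difference to the vaccine. Here the later group is the one given the other vaccine, so the error would favour the test product, provided that day-7 titre rises with day-0 titre. The measurement that would reduce the problem is planned in both booster groups but does not enter this ratio.

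The stakes are limited to a secondary analysis. It is, however, the contrast that sets KD-414 against another third dose, and Analysis of the secondary variables carries similar analyses over to the other immunogenicity markers.

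**Working it through.** **1. The plan's own figure.** Item (5) has no stated precision or power, so the only figure to reproduce is Table 5. Take a margin of -log10(0.67) = 0.1739, a true difference of 0, one-sided alpha of 0.025 and a one-sample (paired) t-test. This gives 34, 39 and 45 at SD 0.35, and 44, 50 and 58 at SD 0.40, for 80, 85 and 90% power. All six cells match. A two-sample normal calculation would need 86 or 112 per group at 90% power. Table 5 therefore serves the comparison with dose 2, not item (5), and this point does not touch it.

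**2. Inputs for item (5).** From Target sample size and rationale: 60 participants given KD-414 and 97 in total, so at most 97 - 60 = 37 others; SD 0.35 (0.40 as sensitivity), which is for IgG-S after dose 2. From the Discussion: 42 days, used as the gap between the two third doses. Not in the documents, and therefore assumed: titre half-life, slope of day-7 on day-0 log titre, their correlation (rho), and individual dose dates.

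**3. Possible shift in the ratio.** The pre-dose difference is D = log10(2) × 42 / half-life. The ratio (other over KD-414) is multiplied by 10^(-slope × D).

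| Half-life (days) | D (log10) | Slope 0 | Slope 0.2 | Slope 0.5 |
|---|---|---|---|---|
| 60 | 0.211 | 1.00 | 0.908 | 0.785 |
| 90 | 0.140 | 1.00 | 0.937 | 0.851 |
| 120 | 0.105 | 1.00 | 0.953 | 0.886 |
| 200 | 0.063 | 1.00 | 0.971 | 0.930 |

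Example: 0.301 × 42/60 = 0.211; 0.5 × 0.211 = 0.105; 10^(-0.105) = 0.785.

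**4. Coverage of the unadjusted interval.** SE = 0.35 × sqrt(1/60 + 1/37) = 0.0732. Coverage under a shift b is Phi(1.96 - b/SE) - Phi(-1.96 - b/SE).

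- b = 0.05: 0.895 (SD 0.40: 0.908)
- b = 0.10: 0.723 (SD 0.40: 0.777)

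**5. Width of the interval.** The unadjusted half-width is t × SE = 0.145 log10, a factor of 1.40 either way (SD 0.40: 0.166, a factor of 1.47). If only 20 decliners are boosted, it is 0.180 (a factor of 1.51). Adjustment multiplies the half-width by sqrt(1 - rho²) and by sqrt(1 + d² / [(1/60 + 1/37) × 95]), where d is the baseline imbalance in SD units. At d = 0.5 the second factor is sqrt(1 + 0.25/4.15) = 1.03.

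| rho | No imbalance | d = 0.5 |
|---|---|---|
| 0 | 0.145 (0%) | 0.150 (+3%) |
| 0.3 | 0.139 (-5%) | 0.143 (-2%) |
| 0.5 | 0.126 (-13%) | 0.130 (-11%) |
| 0.7 | 0.104 (-29%) | 0.107 (-26%) |

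If the day-0 SD is also 0.35, d = 0.5 equals 0.175 log10, which lies inside the range of D in step 3. With equal SDs, slope equals rho, so bias and precision gain vanish together at rho 0 and grow together above it.

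**The case against.** The other side has real strength. The analysis is secondary, in a study that calls itself exploratory and discloses its single-arm, non-randomized design. A separate analysis plan exists and is not shown, and it could name covariates. Fold rise and a dose-interval subgroup are already planned. The 42-day figure comes from a sentence explaining the short follow-up and gives no decliner's dose date.

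What stands against this is that item (5) does specify an estimator, and the natural reading of a geometric mean ratio with no covariate is an unadjusted one. The fold-rise summaries are not specified as a comparison between boosters. The interval subgroup does not repair the ratio either: if decliners are boosted systematically later, interval and group largely coincide.

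Four stronger readings are tempting and are not supported.

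- A reader might infer that the ratio *is* biased. That requires both unequal pre-dose titres and a non-zero slope, and the documents quantify neither. At slope 0 there is no shift.
- A reader might infer that the interval is *too wide*. An unadjusted interval is not wrong for being wider; precision is forgone only to the extent that rho is positive. If bias exists, the more serious harm is under-coverage.
- A reader might compute a power gain. At a true ratio of 0.67, SD 0.35 and rho 0.5, power would go from 66% to 78%. But no test is planned for this ratio, 0.67 is the margin for the comparison with dose 2, and the calculation assumes no baseline imbalance, whereas the bias argument needs one.
- A reader might infer that the trial ignores baseline altogether. It does not; the omission is confined to this ratio and its repeats.

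**Conclusion.** The point holds as a risk, not as a demonstrated bias. The between-booster ratio in item (5) is an unadjusted, non-concurrent, non-randomized comparison that leaves out a pre-dose titre planned in both groups. Different starting titres are likely from the protocol's own account of waning and timing. If day-7 titre rises with day-0 titre, the ratio is liable to favour KD-414 and its interval to under-cover.

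The possible shift runs from none to a factor of 0.785, for a 42-day gap and the assumed half-lives and slopes. A longer gap would enlarge it and a shorter one reduce it. The effect of adjustment on interval width runs from +3% (rho 0, imbalance 0.5 SD) to -29% (rho 0.7, no imbalance). These figures also assume that all 37 decliners are boosted and that the IgG-S SD applies to neutralizing titre. The first sentence of item (5), against undosed participants, is outside this point because that group has no day-0 sample.

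**What to change.** For the second sentence of item (5), specify a linear model of log10 day-7 neutralizing titre on booster group and log10 day-0 titre. Report the back-transformed adjusted geometric mean ratio with its 95% interval, and keep the unadjusted ratio as a sensitivity analysis. Use the same model, with the relevant post-dose titre, where Analysis of the secondary variables repeats this contrast for other quantitative antibody titres that have a day-0 value. State in the plan that differences from self-selection and calendar time remain after adjustment.

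The cost is a sentence or two in the protocol or analysis plan and one extra model; no new sample is needed. Participants without a day-0 titre drop out of the adjusted analysis, and there is little or no gain in precision if the correlation is low.
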